## Abstract

**Background:**

Unemployment is highly prevalent in populations with alcohol and drug dependence and the employment support offered in addiction-treatment programmes is ineffective. Individual Placement and Support (IPS) is an evidence-based intervention for competitive employment. IPS has been extensively studied in severe mental illness and physical disabilities, but there have been no formal randomised controlled trials (RCTs) in alcohol and drug dependence. The Individual Placement and Support for Alcohol and Drug Dependence (IPS-AD) study should determine whether IPS for patients with alcohol use disorder (AUD), opioid use disorder (OUD) and other drug use disorder is effective.

**Design/methods:**

The IPS-AD study is a seven-site, pragmatic, two-arm, parallel-group, superiority RCT. IPS-AD includes a realist process evaluation. Eligible patients (adult, unemployed or economically inactive for at least 6 months and wishing to obtain open job market employment and enrolled in ongoing community treatment-as-usual (TAU; the control condition) in England for AUD, OUD and other drug use disorders) will be randomised (1:1) to receive TAU and any standard employment support, or TAU plus IPS (the experimental condition) for 9 months with up to 4 months of in-work support. The primary outcome measure will be competitive employment status (at least 1 day (7 h)) during an 18-month follow-up, determined by patient-level, trial-data-linkage with national tax and state benefit databases. From meta-analysis, an 18% target difference on this measure of vocational effectiveness (for the experimental intervention) and a two-sided 5% level of statistical significance, will require a minimum target sample of 832 participants to achieve 90% power for a pre-registered, mixed-effects, multi-variable logistic regression model. A maximum-likelihood multiple-imputation approach will manage missing outcome data. IPS-AD has six vocational secondary outcome measures during the 18-month follow-up: (1) total time in competitive employment (and corresponding National Insurance contributions and tax paid); (2) time from randomisation to first competitive employment; (3) number of competitive job appointments; (4) job tenure (length of longest held competitive employment); (5) sustained employment (tenure in a single appointment for at least 13 weeks); and (6) job search self-efficacy. A primary cost-benefit analysis and a secondary cost-effectiveness analysis will be done using the primary outcome and secondary vocational outcomes, respectively and will include addiction treatment and social and health outcomes and their associated reference costs. The process evaluation will address IPS implementation and delivery.

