## Background

Employment is integral to society and a source of economic resource, and an important determinant of personal role identity and life functioning [1]. Job loss and unemployment are associated with stress, poverty, illness and mortality [2–4].

Developed by Becker, Bond and Drake and others at Dartmouth College in the USA, Individual Placement and Support (IPS) is an evidence-based intervention to help people participate in the open competitive labour market [5, 6]. IPS is founded on principles of personal preference, rapid job search, minimal pre-vocational training, and ‘in-work support’ to maintain employment. IPS has been widely studied among people with severe mental illness and physical disability. In these populations, Frederick and VanderWeele reported a meta-analysis of 30 randomised controlled trials (RCTs) of IPS versus standard employment support [7]. In these studies, participants allocated to IPS were more likely to obtain work (relative risk 1.63; 95% Confidence Interval (CI) 1.46–1.82); achieve greater job tenure (defined as duration of longest held competitive employment; Cohen’s *d* 0.55; 95% CI 0.33–0.79); work for longer during follow-up (*d* 0.46; 95% CI 0.35–0.57) and have more income (*d* 0.48; 95% CI 0.36–0.59).

In England in 2017/2018, there was a very high rate of unemployment among people with alcohol and drug dependence (diagnosed as alcohol use disorder (AUD) and opioid, cocaine and other drug use disorder in the *Diagnostic and Statistical Manual of Mental Disorders* (*5th edition*) (*DSM-5*) [8]). Among 75,800 people treated in the community with AUD, 70% were unemployed. Among 141,200 patients with OUD, 85% were unemployed; and among 24,200 patients with another drug use disorder, 68% were unemployed [9]. In contrast with the overall rate of unemployment and economic inactivity in the United Kingdom (UK) in that year – approximately 4% and 21%, respectively^1^ – these are very high rates of unemployment and reflect the ineffectiveness of current employment support provision. In the UK, there are substantial social and economic costs associated with alcohol-related problems (£21.5 billion [10]) and drug-related problems (£20 billion [11]). These include support provided from family and carers; costs associated with the provision of non-elective National Health Service (NHS) hospital treatment (accident and emergency (A&E), outpatient and inpatient care); mortality; loss in productivity; and crime.

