### Sample size

Following preliminary planning, we followed the DELTA^2^ guideline to estimate the minimum sample size for the study [27]. Frederick and VanderWeele’s meta-analysis [7] was used to specify the important and realistic target difference for the primary outcome, with an estimate of its uncertainty. A sensitivity calculation was included if assumptions are mis-specified.

For comparison to the duration of the IPS intervention in IPS-AD, we used the rate of competitive employment status reported by seven superiority trials which evaluated 12 months of IPS (928 participants; outcome rate 0.36 for IPS and 0.13 for TAU; odds ratio (OR) 3.76; 95% CI 2.70 to 5.24). Conservatively, we used the lower bound of the CI (i.e. 2.70; equivalent to an outcome rate of IPS 0.36 and TAU 0.18).

To achieve 90% power to detect this 18% target difference (with a two-sided 5% level of statistical significance and a 20% increase to compensate for missing or inaccurate NINO information) we estimate that 302 participants will be required with AUD and OUD (giving an expected 95% CI estimate for the OR effect within a range from 1.50 to 4.36). If the observed effect falls short of the target difference, we will be able to detect a 15% difference (which we judge is still important) with 83% power (OR 95%, CI 1.24–3.46).

Given the lower number of people in treatment with other drug use disorders, we expect to recruit fewer participants in this group, so it will be realistic to power the analysis at 80%. For the 18% target difference (two-sided, 5% level of significance and with 20% increase for attrition), 228 participants will be needed (95% CI 1.35–4.57).

For the secondary outcome of total time worked, four of the seven trials used for the power calculation for the primary outcome measure in the meta-analysis reported the total number of hours worked (i.e. the sum of all time in all competitive employment during the trial). These four trials recruited 376 participants and the pooled mean difference was 505 h (Hedges’ *g* effect size = 0.54; 95% CI 0.33–0.74). Using this effect size as the realistic mean target difference, the analysis of the secondary outcome for length of competitive employment will have 99% to detect this target difference for the AUD and OUD groups. For the other drug use disorder group, we will be able to detect an effect size ranging from 0.54 to 0.38 with a minimum of 82% power.

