#### Primary vocational effectiveness

The statistical analysis plan (SAP) will be approved by the trial committees and will be published on the Open Science Framework (OSF; www.osf.io) before it is implemented after data-lock. There will be no interim analyses and specified trial-stopping rules. The analysis of the primary outcome (completed in STATA or R; final code to be placed on OSF) will follow the intention-to-treat (ITT) principle and include all patients in the group to which they are allocated. Alpha will be set at 5% for the primary and secondary outcomes (with associated 95% CIs). The distributions of scale and count measures may be non-normal (skewed), so that test statistics and effect sizes may be computed following appropriate transformation (e.g. natural log to obtain a geometric mean).

Data from all sites will be pooled and the superiority effectiveness estimate for the IPS intervention (adjusted OR and CI) will be determined using a mixed-effects, multi-variable logistic regression model. The model will include the stratification variables and a random intercept for each site to account for clustering. A maximum-likelihood multiple-imputation approach will be used for the management of missing data with a sensitivity comparison to the complete case dataset.

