#### Analysis of secondary vocational and alcohol and drug-treatment-related outcomes

The ITT analysis of the secondary vocational and clinical outcomes will be done using appropriate mixed-effects regression models according to each measure (i.e. linear for time-based (total time in employment and treatment); Poisson for count-based (number of appointments; days of alcohol and drug use; number of treatment episodes); logistic for binary outcomes (sustained employment; *DSM-5 remission*); ordinal for treatment exit status; and proportional-hazards (for time to first employment) with measure-appropriate covariates. These models will include site and employment history stratification factors and may include other background variables. Exploratory models will also be separately done for AUD, OUD and other drug use disorder groups. A causal mediation framework analysis will be used to determine the evidence for a theoretical mechanism of change for the IPS intervention using the JSSE-B as a mediator of competitive employment.

After completing the analysis and reporting of the primary and secondary analyses, we plan to undertake exploratory longer-term analyses using the national registry data at 3 years and 6 years – subject to approval for a protocol amendment.

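### The abstract ties 832 participants to 90% power for the pooled primary model, but 832 is the sum of three diagnosis-specific sample sizes and the pooled model has over 99.9% power

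*Protocol article*

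**What the plan says.** The abstract (Design/methods) links the total to the primary analysis: an 18-point target difference at two-sided 5% "will require a minimum target sample of 832 participants to achieve 90% power for a pre-registered, mixed-effects, multi-variable logistic regression model".

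The Sample size section derives its numbers by diagnosis. For rates of 0.36 (IPS) and 0.18 (TAU) at 90% power, "we estimate that 302 participants will be required with AUD and OUD". For other drug use disorder, where fewer recruits are expected, power is set at 80% and "228 participants will be needed". Each figure includes a 20% increase for loss. The section closes by giving 832 as the minimum total.

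The primary analysis is a single model. Under Primary vocational effectiveness, "Data from all sites will be pooled and the superiority effectiveness estimate" comes from one mixed-effects logistic regression with the stratification variables and a random intercept for site. The only diagnosis-specific models in the article are in the section on secondary vocational and treatment-related outcomes: "Exploratory models will also be separately done for AUD, OUD and other drug use disorder groups".

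**The concern.** The abstract and the Sample size section describe two different designs. In the abstract, one pooled comparison needs 832 people for 90% power. In the Sample size section, three comparisons are each sized on their own, one of them at 80%. Both cannot be the basis of the same total.

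Two things follow. A reader of the abstract gets the wrong required size and the wrong power for the primary analysis, and the article never states that analysis's actual power. Also, the comparisons that set the recruitment target do not appear as confirmatory analyses anywhere in the article, so the reason for recruiting 832 and the planned use of the data do not match.

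**Working it through.** **Inputs, all from the article**
- Rates 0.36 and 0.18, difference d = 0.18 (Sample size).
- Two-sided 5% and a 20% increase: "with a two-sided 5% level of statistical significance and a 20% increase to compensate for missing or inaccurate NINO information".
- Power 90% for AUD and OUD, 80% for other drug use disorder (Sample size).
- 1:1 individual randomisation, stratified by site, diagnosis and work history (Procedure).

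**Step 1: reproduce the plan's figures.** Two-proportion formula, pooled variance under the null, no continuity correction, mean rate p̄ = 0.27:

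n per arm = [z(0.975)·√(2p̄(1−p̄)) + z(power)·√(p₁(1−p₁) + p₂(1−p₂))]² / d²

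- √(2 × 0.27 × 0.73) = √0.3942 = 0.6279, and 1.960 × 0.6279 = 1.2306.
- √(0.36 × 0.64 + 0.18 × 0.82) = √0.378 = 0.6148.
- 90% power: (1.2306 + 1.2816 × 0.6148)² / 0.0324 = 125.75, so 126 per arm. 252 × 1.2 = 302.4 (stated 302).
- 80% power: (1.2306 + 0.8416 × 0.6148)² / 0.0324 = 94.3, so 95 per arm. 190 × 1.2 = 228 (stated 228).

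Both stated sizes reproduce. The variants tried (continuity correction, unpooled variance, dividing by 0.8 instead of multiplying by 1.2) do not give both.

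**Step 2: rebuild the total.** 302 + 302 + 228 = 832 exactly. The phrase about AUD and OUD could be read as one combined group, but 302 + 228 is only 530. So 302 applies to each.

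**Step 3: what one pooled comparison needs.** The 90% result in Step 1 already answers this: 252 evaluable, or about 302 randomised on the plan's own inflation (252 / 0.8 = 315 if 20% are lost).

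**Step 4: what 832 gives the pooled comparison.** Power = Φ{[d√n − 1.2306] / 0.6148}, with n per arm.

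| Evaluable | n per arm | Power, 0.36 v 0.18 | Difference detectable at 90% power (TAU 0.18) |
|---|---|---|---|
| 832 × 0.8 = 666 | 333 | 99.96% | 10.6 points |
| 832 / 1.2 = 693 | 347 | 99.97% | 10.4 points |
| 832, no loss | 416 | above 99.99% | 9.4 points |

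A Wald calculation on the log odds ratio, closer to the logistic model, also gives more than 99.9% at 666 evaluable: ln(2.5625) = 0.941, SE = 0.183, and Φ(0.941/0.183 − 1.96) = Φ(3.19) = 99.93%.

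**Step 5: could clustering explain 832?** The article gives no intraclass correlation or design effect, and randomisation is individual within site. Bringing 832 down to 90% pooled power would take a design effect of about 666/252 = 2.64 to 693/252 = 2.75. Nothing in the article suggests one.

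**The case against.** The best defence is that the misstatement is on the safe side. The pooled model far exceeds 90% power at the target, so its type I error, estimate and validity are untouched. The Sample size section sets out the diagnosis-specific derivation openly, so a reader of the full text can see where 832 comes from. This stands, and it limits how serious the point is. It does not make the abstract's sentence correct, and that sentence does not describe the subgroup design either, because one of the three groups is powered at 80%.

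Another defence is that the larger total has other uses. The Sample size section does mention mediation analysis and longer-term follow-up, but as reasons to recruit beyond 832, not as its basis.

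Some stronger readings are tempting, and the article does not support them:
- *The diagnosis-specific primary comparisons have been demoted to exploratory.* The exploratory sentence is in the secondary-outcomes section and does not name the primary outcome. The analysis plan is not shown and may settle their status. What can be said is that this article gives them no confirmatory role.
- *The trial has only 0.9 × 0.9 × 0.8 = 65% power.* That would be the chance of significance in all three groups at the target. The article nowhere makes this a criterion of success.
- *Power is poor at the effect in the wider literature.* The Background reports that "participants allocated to IPS were more likely to obtain work (relative risk 1.63", but turning this into power needs a control rate. At 693 evaluable, pooled power is 82% with TAU 0.13, 94% with 0.18 and 98% with 0.22. The answer depends on that assumption, and it questions the target effect, which is a separate issue.
- *Significance below 15 to 18 points would mislead.* That a significant result does not establish the target difference is true of any well-powered superiority trial. The plan already reports an adjusted odds ratio with its interval, and it nowhere calls smaller effects unimportant.

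**Conclusion.** The point holds. The abstract's required size and power do not belong to the pooled primary model. That model needs about 302 randomised for 90% power, and at 832 it has over 99.9% power for 18 points and 90% power for about 10.4 to 10.6 points. The 832 comes from three within-diagnosis comparisons at 90%, 90% and 80% power, which the article does not carry into a confirmatory analysis.

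This rests on the plan's rates of 0.36 and 0.18, on 666 to 693 evaluable participants, and on a two-proportion approximation to the mixed-effects model with no design effect. The conclusion does not depend on the exact loss rate. Because the error is conservative and leaves the primary test valid, it should be corrected but is not a must-fix.

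**What to change.** 1. Reword the abstract sentence and the closing paragraph of the Sample size section: 832 = 302 + 302 + 228, giving 90%, 90% and 80% power within AUD, OUD and other drug use disorder for 18 points.
2. State the pooled primary model's own power beside it: over 99.9% for 18 points and 90% for about 10 points, with the control rate and loss assumed.
3. Before data-lock, reconcile the Sample size section with the two analysis sections by stating the status of the diagnosis-specific contrasts on the primary outcome. Two options are defensible:
   - pre-specify them from the pooled model, with a treatment-by-diagnosis interaction test on two degrees of freedom (diagnosis has three levels) and multiplicity control across the three contrasts; testing them only after a significant pooled result would not by itself control error among them; or
   - call them exploratory and reword the sample-size rationale to match.

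Which option to take is a design choice on which statisticians can differ. The cost is wording and, under the first option, minor analysis work. No extra participants are needed.

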**Discussion:**

The IPS-AD study is the first large-scale, multi-site, definitive, superiority RCT of IPS for people with alcohol and drug dependence. Findings from the study will have substantial implications for service delivery.

**Trial registration:**

ISRCTN Registry, ID: ISRCTN24159790. Registered on 1 February 2018.

## Background

Employment is integral to society and a source of economic resource, and an important determinant of personal role identity and life functioning [1]. Job loss and unemployment are associated with stress, poverty, illness and mortality [2–4].

Developed by Becker, Bond and Drake and others at Dartmouth College in the USA, Individual Placement and Support (IPS) is an evidence-based intervention to help people participate in the open competitive labour market [5, 6]. IPS is founded on principles of personal preference, rapid job search, minimal pre-vocational training, and ‘in-work support’ to maintain employment. IPS has been widely studied among people with severe mental illness and physical disability. In these populations, Frederick and VanderWeele reported a meta-analysis of 30 randomised controlled trials (RCTs) of IPS versus standard employment support [7]. In these studies, participants allocated to IPS were more likely to obtain work (relative risk 1.63; 95% Confidence Interval (CI) 1.46–1.82); achieve greater job tenure (defined as duration of longest held competitive employment; Cohen’s *d* 0.55; 95% CI 0.33–0.79); work for longer during follow-up (*d* 0.46; 95% CI 0.35–0.57) and have more income (*d* 0.48; 95% CI 0.36–0.59).

In England in 2017/2018, there was a very high rate of unemployment among people with alcohol and drug dependence (diagnosed as alcohol use disorder (AUD) and opioid, cocaine and other drug use disorder in the *Diagnostic and Statistical Manual of Mental Disorders* (*5th edition*) (*DSM-5*) [8]). Among 75,800 people treated in the community with AUD, 70% were unemployed. Among 141,200 patients with OUD, 85% were unemployed; and among 24,200 patients with another drug use disorder, 68% were unemployed [9]. In contrast with the overall rate of unemployment and economic inactivity in the United Kingdom (UK) in that year – approximately 4% and 21%, respectively^1^ – these are very high rates of unemployment and reflect the ineffectiveness of current employment support provision. In the UK, there are substantial social and economic costs associated with alcohol-related problems (£21.5 billion [10]) and drug-related problems (£20 billion [11]). These include support provided from family and carers; costs associated with the provision of non-elective National Health Service (NHS) hospital treatment (accident and emergency (A&E), outpatient and inpatient care); mortality; loss in productivity; and crime.

Aside from a single, small-scale pilot study of IPS for patients receiving medication treatment for OUD [12], IPS has not been evaluated for people with alcohol and drug dependence. The gap was identified by a UK-government-commissioned independent review [13], and the Work and Health Unit (a collaboration between the Department for Work and Pensions (DWP) and the Department of Health and Social Care (DHSC)) invited researchers from Public Health England (PHE) to submit a proposal for a definitive, multi-centre, RCT of IPS.

This article describes the protocol for the Individual Placement and Support for people with Alcohol and Drug dependence (IPS-AD) trial.

## Methods

### Design

IPS-AD is a pragmatic, multi-centre, two-arm, parallel-group, superiority RCT, with a realist process evaluation. The aim of the study is to determine the effectiveness of IPS to help people with AUD, OUD and other drug use disorders to obtain employment in the open competitive job market. These questions will be answered by pre-registered analyses of primary and secondary outcomes recorded across an 18-month follow-up after randomisation (Fig. 1). There are also planned analyses of outcome mediation and effectiveness over the longer term.

**Fig. 1 Fig1:**
[figure not shown]
Consolidated Standards of Reporting Trials (CONSORT) flow of participants

After enrolment, all study participants will continue to be enrolled in addiction treatment (co-ordinated by a clinician called a keyworker) and may receive standard employment support (conventionally termed treatment-as-usual (TAU) – the control condition), or they will continue to be enrolled in addiction treatment, and may receive standard employment support, and enrolled in IPS – the intervention condition.

The study will be reported following the CONSORT Guideline (Consolidated Standards of Reporting Trials; http://www.consort-statement.org/) extension for non-medication trials [14] and the Template for Intervention Description and Replication (TIDieR) Checklist for reporting interventions [15]. This protocol has been written following the Standard Protocol Items: Recommendations for Interventional Trials (SPIRIT) Checklist for intervention trials [16] – see Additional file 1: Table S1.

IPS-AD will be conducted following the principles of the Declaration of Helsinki [17], the Medical Research Council Guidelines for Good Clinical Practice [18], and the NHS Research Governance Framework [19]. Participants will have the right to withdraw from the trial at any time without giving a reason. There is no anticipated harm so no compensation arising from trial participation.

